**Fig. 1 Fig1:**
[figure not shown]
Study flowchart. CN, cytoreductive nephrectomy; IMDC, International mRCC Database Consortium; Ipi, ipilimumab; mRCC, metastatic renal cell carcinoma; Nivo, nivolumab; KPS, Karnofsky performance status

Candidates for CN are patients with good performance status (Karnofsky performance status ≥ 80%) and less than three IMDC risk features and whose primary tumor could be surgically removed. Metastasectomy can be performed when the metastatic sites can be surgically removed. All patients eligible for ICI therapy will receive four cycles of intravenous nivolumab (3 mg/kg) plus ipilimumab (1 mg/kg) every 3 weeks as the induction phase, followed by a response evaluation. After the induction phase, intravenous nivolumab (3 mg/kg) will be administered 6 times every 2 weeks as the maintenance phase, followed by response evaluation. Nivolumab monotherapy will be maintained for a maximum of 2 years for those without adverse side effects. During ICI therapy, adverse events will be evaluated once per cycle. Patients will discontinue ICI therapy when they develop serious adverse events, including grade 3 or worse, according to the Common Terminology Criteria for Adverse Events version 5.0 (CTCAE v 5.0). In the upfront CN group, the induction phase will be within 6 weeks of surgery, whereas in the deferred CN group, surgery will be performed within 6 weeks of the induction phase. The study will be conducted over a period of 5 years.

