### Sample size justification

Two prospective RCTs, PROBE (NCT04510597) and NORDICSUN (NCT03977571), are currently ongoing, but do not include an upfront CN arm. We determined the sample size based on the most recent real-world data that analyzed the intermediate/high risk group of mRCC patients stratified into upfront CN, deferred CN, and systemic treatment group [17]. To determine the required sample size for the study, we utilized two calculators for two-group survival analysis [18]. For Calculator 1, with a two-tailed alpha level (*α*) set at 0.05 and a beta level (*β*) of 0.2, along with a proportion of subjects in Group 1 (upfront and deferred CN) of 0.66 and a proportion in Group 0 (ICIs only) of 0.34, the relative hazard was set at 0.37. The calculated number of events needed to achieve 80% power was 35. For Calculator 2, with the total number of events set at 35, and assuming a baseline event rate of 0.53 and a median survival time in Group 0 (ICIs only) of 1.3 years, along with a censoring rate of 0.1 and a planned average length of follow-up of 5 years, the sample sizes required for each group were determined. Therefore, a total of 57 subjects were needed for the study.

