## Discussion

The optimal use of CN in mRCC settings remains unclear, especially in ICI therapy settings [19], where the most recent evidence has been generated in the TKI era [19]. Although the potential of CN in the primitive IO era has drawn attention, no studies have thoroughly evaluated the role of CN in ICI therapy in patients with mRCC, where recent guidelines have moved away from TKI monotherapy in favor of ICI-based combinations. This is the first study to comprehensively incorporate both upfront and deferred CN and compare both with ICI therapy, redefining the role and timing of surgeries in mRCC. Because oncologic surgery can effectively control cancer by removing tumor cells [20], it should be considered as a treatment option for mRCC in selected patients, weighing the benefits and risks tailored to each patient. Moreover, CN may reduce the cost of ICI therapy, allowing for therapeutic holidays [19]. As patient selection is critical for expanding the role of CN in the contemporary IO era [21], the objective of this study is to develop biomarkers for patient selection for CN by analyzing gene mutation profiles and microbiomes. Due to the small number of study population, there could be some difficulties in drawing conclusions for discovery of biomarkers. Therefore, we will first achieve our primary endpoint, OS, and will expand the study for other analysis. Furthermore, the decision to perform CN should be discussed by a multidisciplinary team and clearly explained to the patients during shared decision-making sessions.

This study was registered at ClinicalTrials.gov on March 3, 2023. Patient accrual began in December 2022. Follow-up will be performed for at least 5 years or until death.

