## Trial status

Recruitment of participants started in July 2023 and will be completed in December 2027. The manuscript reports protocol version 1.0 (January 2, 2023).

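### The stated 5-year study period conflicts with recruitment to December 2027 and with 5 years of follow-up; if it set the survival data cut, power would be about 60–67%, not 80%

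*Protocol article*

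**What the plan says.** Four places in the protocol article bear on calendar time and follow-up.

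- Study timeline, end of the text below Fig. 1: "The study will be conducted over a period of 5 years".
- Sample size justification: the number of patients is calculated with "a planned average length of follow-up of 5 years".
- Trial status: "Recruitment of participants started in July 2023 and will be completed in December 2027".
- Discussion, last paragraph: "Follow-up will be performed for at least 5 years or until death". The same paragraph dates the start of accrual to December 2022, not July 2023.

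The sample size section also states: "The calculated number of events needed to achieve 80% power was 35". It then arrives at 57 subjects; the Abstract gives 55.

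**The concern.** Recruitment takes about 4.4 to 5 years, depending on which start date is used. A study lasting 5 years in total would therefore close between December 2027 and about July 2028, and the last entrants would have between 0 and about 7 months of follow-up. That cannot produce a 5-year average, still less 5 years for each patient. This follows from the dates alone.

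OS is the primary endpoint. For the planned hazard ratio and allocation, the power of the log-rank comparison is determined by the number of deaths, and that number depends on when the data are cut. The 57 patients yield the planned 35 deaths only if the 5-year average is delivered. A reader of the article cannot tell whether the trial will have the power it claims.

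**Working it through.** **Inputs (Sample size justification).** Two-sided alpha 0.05 and power 80%; hazard ratio 0.37; proportions 0.66 (upfront and deferred nephrectomy) and 0.34 (checkpoint inhibitors only); event rate 0.53 per year in the inhibitor-only group, consistent with the stated 1.3-year median (ln 2 / 1.3 = 0.533); censoring rate 0.1; average follow-up 5 years. The article gives no unit for the censoring rate. I take it as per year, because that reproduces the plan's 57.

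**Step 1: reproduce the events.** Schoenfeld: 7.849 / (0.66 × 0.34 × (ln 0.37)²) = 7.849 / (0.2244 × 0.9885) = 35.4. The plan's 35 reproduces; exactly 35 deaths give 79.6% power.

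**Step 2: reproduce the patients.** With death rate h, censoring rate c and follow-up T, P(death) = h/(h + c) × (1 − exp(−(h + c)T)). At T = 5 and c = 0.1:

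- inhibitor-only group, h = 0.53: 0.805
- nephrectomy groups, h = 0.53 × 0.37 = 0.196: 0.512
- weighted: 0.34 × 0.805 + 0.66 × 0.512 = 0.611
- patients: 35 / 0.611 = 57.2

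The plan's arithmetic is sound, and the 57 depends directly on the 5-year input.

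**Step 3: put the calendar in.** Assume uniform accrual, so that follow-up is uniform from a to b years. The mean of P(death) is then h/(h + c) × [1 − (exp(−(h + c)a) − exp(−(h + c)b)) / ((h + c)(b − a))]. Power is Φ(|ln 0.37| × √(0.2244 × deaths) − 1.96).

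Example, accrual December 2022 to December 2027 and close December 2027 (a = 0, b = 5): 0.586 and 0.317 in the two groups, weighted 0.408; 57 × 0.408 = 23.3 deaths; Φ(0.994 × √(0.2244 × 23.3) − 1.96) = 62%.

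| Accrual and data cut (n = 57) | Mean follow-up, years | Deaths, c = 0.1 | Power | Deaths, c = 0 | Power |
|---|---|---|---|---|---|
| Jul 2023–Dec 2027, cut Dec 2027 (0–4.42) | 2.2 | 21.8 | 60% | 24.4 | 64% |
| Dec 2022–Dec 2027, cut Dec 2027 (0–5) | 2.5 | 23.3 | 62% | 26.2 | 67% |
| Jul 2023–Dec 2027, cut Jul 2028 (0.58–5) | 2.8 | 25.7 | 67% | 29.0 | 72% |
| Jul 2023–Dec 2027, at least 5 years each (5–9.42) | 7.2 | 37.8 | 83% | 47.0 | 90% |

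The c = 0 columns drop the additional censoring and keep only the censoring caused by the data cut. With 55 patients and c = 0.1, the three short timelines give 58–65% power and the 5-year minimum gives 81%. Treating the mean follow-up as a fixed time for every patient, as the plan's own calculation does, gives 24–28 deaths and 64–70% on the short timelines (n = 57).

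**Step 4: when 35 deaths would be expected.** Solving n × (mean probability of death) = 35 with c = 0.1 gives 2.9–3.2 years after the last entry for 57 patients and 3.6–3.8 years for 55, depending on the accrual start. Both fall inside the 5-year minimum of the Discussion.

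**The case against.** The strongest objection is that no loss of power has been shown. The two places that speak of patient follow-up, the sample size section and the Discussion, are both compatible with 80% power. The 5-year sentence closes a paragraph on treatment and the timing of surgery and mentions neither OS nor a data cut. It may describe enrolment: December 2022 to December 2027 is exactly 5 years, and with follow-up continuing afterwards the statements agree.

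Much of this stands. A reader might infer that the trial is underpowered as planned, or that a 5-year close is the analysis rule because nothing ties the OS analysis to the 35th death. The documents support neither inference. The Discussion points the other way, and a condensed article may leave the timing of analysis to a fuller document, so its silence on an event trigger proves nothing.

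The objection does not remove the conflict. The sentence speaks of conducting the study, not of enrolling patients. The enrolment reading also needs the December 2022 start, whereas Trial status gives July 2023. A reader must choose between the article's statements to know how much information the primary analysis will have.

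It is also fair to object that 60–67% is not the full range on the short timelines. It depends on uniform accrual and on how censoring is handled; the alternatives above reach 72%. None reaches 80%.

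**Conclusion.** The point holds as an internal contradiction with a conditional consequence. As a total duration, 5 years is incompatible with recruitment to December 2027 combined with 5 years of average or minimum follow-up.

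If that period sets the OS data cut, expect about 22–26 deaths and 60–67% power with 57 patients, or 24–29 deaths and 64–72% without the additional censoring. If the Discussion's minimum follow-up governs, expect about 38 deaths and 83%, with no shortfall.

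These figures rest on the plan's hazard ratio and event rate, exponential survival, uniform accrual and a censoring rate read as per year. The conflict itself rests only on the stated dates and durations. It needs correcting because it decides whether the claimed power for the primary endpoint holds.

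**What to change.** 1. Under Study timeline, replace the 5-year period with one that covers recruitment plus the follow-up in the sample size section and the Discussion, or state that the 5 years is the enrolment period. Settle the start of accrual (December 2022 or July 2023) at the same time.
2. Tie the single OS analysis to a cut-off that delivers the planned information. Either of these would do:
   - the 35th death, expected about 3 years after the last entry with 57 patients (around the turn of 2030 to 2031 if recruitment ends in December 2027) or about 3.6–3.8 years with 55;
   - 5 years after the last entry, matching the minimum follow-up in the Discussion (about December 2032).
3. If a 5-year close is really intended, restate expected deaths and power at the values above. Keeping 35 deaths under that close would take roughly 78 to 91 patients (35 / 0.451 to 35 / 0.383).

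The first two changes are a matter of wording. Their cost is a data cut later than a 5-year close would give, but within follow-up the article already promises and with no extra patients.

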### Sample collection

Tumor tissue, blood, urine, and stool specimens for translational biomarker research will be sampled at the baseline visit, during surgery, 3 months after induction therapy, and 3 months after maintenance therapy. Embedded future studies will have their specific protocol and will obtain specific approval from the ethics committee separately. The tumor tissue from the participants will be obtained from a core needle biopsy sample (20 mg) or a surgically excised sample (1 g) of the viable tumor portion confirmed by the pathologist. Blood (10 mL for plasma) will be drawn when a medically required blood draw is present. Midstream urine (10 mL) and fecal (2–3 cc) samples will be collected from patients using the information leaflet provided. Samples will be collected 3–4 times, and an overview of the planned sample collection is shown in Tables 2, 3, and 4. All samples will be anonymously labeled with a pseudo-patient study identifier.

**Table 2 Tab2:** Study schedule of visits, and sampling of upfront cytoreductive nephrectomy group (Group A)

Time	0	*X*	*X* + 4 months	*X* + 7 months
Visit	Baseline visit	During surgery	After ICI induction phase (4 cycles)	After ICI maintenance phase (6 cycles)
Blood sample	O	O	O	O
Urine sample	O	O	O	O
Stool sample	O	O	O	O
Tumor tissue sample	O	O

**Table 3 Tab3:** Study schedule of visits, and sampling of deferred cytoreductive nephrectomy group (Group B)

Time	0	*X*	*X* + 3 months	*X* + 4 months	*X* + 7 months
Visit	Baseline visit	Before ICI therapy	After ICI induction phase (4 cycles)	During surgery	After ICI maintenance phase (6 cycles)
Blood sample	O		O	O	O
Urine sample	O		O	O	O
Stool sample	O		O	O	O
Tumor tissue sample	O			O

**Table 4 Tab4:** Study schedule of visits, and sampling of immune checkpoint inhibitor therapy group (Group C)

Time	0	*X*	*X* + 3 months	*X* + 6 months
Visit	Baseline visit	Before ICI therapy	After ICI induction phase (4 cycles)	After ICI maintenance phase (6 cycles)
Blood sample	O		O	O
Urine sample	O		O	O
Stool sample	O		O	O
Tumor tissue sample	O			

### Public and patient involvement statement

Neither public nor patients were involved in the protocol development and study design.

### Sample size justification

Two prospective RCTs, PROBE (NCT04510597) and NORDICSUN (NCT03977571), are currently ongoing, but do not include an upfront CN arm. We determined the sample size based on the most recent real-world data that analyzed the intermediate/high risk group of mRCC patients stratified into upfront CN, deferred CN, and systemic treatment group [17]. To determine the required sample size for the study, we utilized two calculators for two-group survival analysis [18]. For Calculator 1, with a two-tailed alpha level (*α*) set at 0.05 and a beta level (*β*) of 0.2, along with a proportion of subjects in Group 1 (upfront and deferred CN) of 0.66 and a proportion in Group 0 (ICIs only) of 0.34, the relative hazard was set at 0.37. The calculated number of events needed to achieve 80% power was 35. For Calculator 2, with the total number of events set at 35, and assuming a baseline event rate of 0.53 and a median survival time in Group 0 (ICIs only) of 1.3 years, along with a censoring rate of 0.1 and a planned average length of follow-up of 5 years, the sample sizes required for each group were determined. Therefore, a total of 57 subjects were needed for the study.

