**Discussion:**

This study is one of the few prospective randomized trials to evaluate the benefit of CN in the treatment of synchronous mRCC in the IO era. The SEVURO-CN trial will help identify the role and timing of CN, thereby rediscovering the value of CN.

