### Primary endpoint

The primary endpoint is OS (in months) compared between patients receiving upfront CN, deferred CN, and ICIs only.

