### Study timeline

After completing the recruitment procedure, clinical and pathological data were collected (Table 1).

**Table 1 Tab1:** Clinical and pathological data

Clinical data				Pathological data
Baseline	Surgery-related	ICI therapy-related	Oncological outcome	
Age	OR note (including any intraoperative events)	Dosage	Overall survival	Pathological TNM staging
Sex	EBL	Cycle	Progression-free survival	Cell type
Height	Surgical morbidity (according to CDC)	Toxicities (graded by CTCAE v5.0)	Objective response rate (according to RECIST v1.1)	ISUP nuclear grade
Weight		Total administration periods		
BMI		Cause of discontinuation		
BSA				
KPS				
IMDC risk feature				
Clinical TNM staging				
Metastatic sites				

*BMI* body mass index, *BSA* body surface area, *CDC* Clavien–Dindo classification, *CTCAE* Common Terminology Criteria for Adverse Events, *EBL* estimated blood loss, *IMDC* International mRCC Database Consortium, *ISUP* International Society of Urologic Pathologists, *KPS* Karnofsky Performance Status, *OR* operating room, *RECIST* Response Evaluation Criteria for Solid Tumors

A flowchart of the study is shown in Fig. 1. Patients will be evaluated for eligibility for surgery. If they are not eligible for surgery, they will start ICI therapy (induction phase). Then, they will be assessed for whether they are eligible for surgery. If not, they will continue with ICI therapy (maintenance phase) (Group C). If they are eligible for surgery, they will be randomly allocated to the deferred CN group (Group B) or ICIs only. If they are eligible for surgery at the first visit, they will be randomly allocated to the upfront CN Group A (group A) or the deferred CN group (Group B). Patients will be randomly allocated in a 1:1 ratio using a computer-generated allocation sequence by a local project nurse. The randomization will be performed on an institutional basis to prevent bias.

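### The 80% power is calculated for pooled CN versus ICIs only, but the declared primary comparison has three groups and about 70% power on the same inputs

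*Protocol article*

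**What the plan says.** The protocol article's Sample size justification states that "we utilized two calculators for two-group survival analysis". The calculation was run "with a two-tailed alpha level (*α*) set at 0.05 and a beta level (*β*) of 0.2". Its two groups are defined by "a proportion of subjects in Group 1 (upfront and deferred CN) of 0.66 and a proportion in Group 0 (ICIs only) of 0.34". The assumed HR is 0.37, and the result reads: "The calculated number of events needed to achieve 80% power was 35". A second step turns this into 57 subjects.

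The Primary endpoint section defines OS as "compared between patients receiving upfront CN, deferred CN, and ICIs only". Study design asks whether upfront or deferred CN improves outcomes over ICIs alone. The Discussion paragraph of the Abstract adds: "The SEVURO-CN trial will help identify the role and timing of CN".

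Statistical analysis gives a log-rank test and a two-sided 0.05 level. It does not pool the CN arms or say which comparison is primary.

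On allocation, Study timeline says: "Patients will be randomly allocated in a 1:1 ratio using a computer-generated allocation sequence". Patients eligible for surgery at the first visit are randomized to A (upfront) or B (deferred). Those who become eligible only after induction are randomized to B or C (ICIs only). Those still ineligible go to C without randomization.

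**The concern.** The pooled contrast appears only in the sample size paragraph. The primary comparison has three groups, and the stated aims also cover each CN strategy against ICIs and the timing of surgery. A reader who sees 80% power next to a three-group primary endpoint will attach the figure to that endpoint.

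At stake is how the result is read. If the trial is analysed as the primary endpoint describes, the chance of missing an effect of the planned size is nearer 30% than 20%. An inconclusive comparison of upfront with deferred CN would be the likely result even if timing mattered. With no contrast tied to the sizing, it is also unclear which test the 35 events are meant to support.

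**Working it through.** **Inputs, all from Sample size justification:** two-sided alpha 0.05, power 80%, shares 0.66 and 0.34, HR 0.37, control hazard 0.53 per year (ln 2/1.3 = 0.533), censoring 0.1 (read as per year), follow-up 5 years.

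**1. Reproduce the plan's figures (pooled A+B versus C).**
- Events (Schoenfeld) = (1.960 + 0.842)² / (0.66 × 0.34 × (ln 0.37)²) = 7.849 / (0.2244 × 0.9885) = 35.4. The plan gives 35; power at 35 events is 79.6%.
- Probability of an observed death = λ/(λ+0.1) × (1 − exp(−5(λ+0.1))). For C, λ = 0.53 gives 0.805. For CN, λ = 0.53 × 0.37 = 0.196 gives 0.512.
- Weighted: 0.66 × 0.512 + 0.34 × 0.805 = 0.611. N = 35/0.611 = 57.2. The plan gives 57.

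Both figures reproduce, for this contrast.

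**2. Three-group log-rank test, 35 events.** If both CN arms have HR 0.37, the noncentrality is that of the pooled test, 35 × 0.2244 × 0.9885 = 7.76, now spread over 2 degrees of freedom. Against the critical value 5.99, power is 0.70. A simulation (4,000 runs, 19 per arm, same hazards and censoring) gives 74%, and 83% for the pooled test. The loss is about 9 points either way. Reaching 80% by the formula would take about 44 events, or about 71–72 patients.

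**3. One CN arm versus C, about 19 per arm.** Events = 19 × (0.805 + 0.512) = 25.0. Power = Φ(√(25.0/4) × 0.994 − 1.960) = Φ(0.53) = 0.70 (68% by simulation). At alpha 0.025 it is about 60%.

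**4. Upfront versus deferred.** Events = 38 × 0.512 = 19.4. The HR detectable with 80% power is exp(−2 × 2.802/√19.4) = 0.28. At an assumed HR of 0.6, power = Φ(√(19.4/4) × 0.511 − 1.960) = 0.20. Across assumed HRs of 0.5 to 0.8 it runs from about 33–39% down to about 7%.

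**5. If all three pairs were tested separately at 0.05.** With equal groups and no true differences, the family-wise error is the probability that the range of three standard normals exceeds 1.960 × √2 = 2.77, which is about 12%.

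**6. Sensitivity to C's share.** The two 1:1 randomizations do not produce 66:34, because C's share depends on how many patients are ineligible for surgery. With an assumed C share of 0.20, events needed = 7.849/(0.80 × 0.20 × 0.9885) = 49.6. Events expected at N = 57 are 57 × (0.80 × 0.512 + 0.20 × 0.805) = 32.5. Power = Φ(√(32.5 × 0.16) × 0.994 − 1.960) = 0.62.

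**The case against.** The sample size section is correct for what it computes. It labels Group 1 as both CN arms and calls the method two-group, and it claims 80% power for nothing else. That stands: this is a mismatch between sections, not an arithmetic error.

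Three stronger readings are tempting, and the document does not support them.
- **The plan inflates type I error to 12%.** Statistical analysis specifies no pairwise tests. One 2-degree-of-freedom log-rank test at 0.05 fits the primary endpoint wording and needs no adjustment. The 12% is conditional on a choice the article neither makes nor rules out, and a multiplicity rule may sit in a document not shown. Its absence is not part of this point.
- **The trial promises to settle timing.** The Abstract claims only to help identify it, and no powered hypothesis of upfront against deferred CN is stated.
- **The sizing would be sound if randomized A+B were tested against randomized C.** That contrast is not available. Patients eligible at the first visit can never be allocated to C, A is never randomized against C, and some of C is not randomized at all. Making C a randomized third would redesign the allocation.

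The size of the shortfall also rests on assumptions, and the formula's 70% is an approximation that simulation puts nearer 74%. None of this removes the core of the point. The primary comparison and the sizing basis are both stated in this article, and they disagree.

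**Conclusion.** The point holds as a mismatch. The stated 80% applies to pooled CN versus ICIs only at a 66:34 split, and no section declares that contrast primary. Under either reading of the three-group endpoint, a single overall test or one CN arm against C, power at the plan's own effect size is about 70% (68–74% when the simulations are included). Upfront versus deferred CN is far from powered: 80% is reached only at an HR of about 0.28 or stronger.

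The figures assume about 19 patients per arm and HR 0.37 in each CN arm. The document gives neither, nor an HR for timing or an expected share for C, so the timing HRs and the 20% share are illustrations. If the effect of a single CN arm were weaker, at HRs of 0.5, 0.6 or 0.7, power against C would fall to about 44%, 27% or 16%.

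**What to change.** - In Primary endpoint and Statistical analysis, name one primary contrast that agrees with Sample size justification and with the allocation in Study timeline.
- In Sample size justification, state that 80% power applies only to the pooled contrast at a 66:34 split. Give the lower figures for the three-group and pairwise comparisons, with their assumptions.
- Label the remaining comparisons secondary. Report upfront versus deferred CN as an HR with 95% CI, as estimation and not as a powered test.
- If the pooled contrast is kept as primary, state that it is not fully randomized under the present allocation, and restate its power for the share of patients expected in C.

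The cost is wording and a less favourable power statement, with no extra patients. Keeping the three-group test as primary and restoring 80% power would be a different choice, and would need about 71–72 patients on the plan's inputs.
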